## Abstract

**Background:**

Relatives of people diagnosed with suicidal behavior disorder (SBD) feel guilty, afraid, hopeless, depression and anxiety. It is necessary to help the relatives of people with SBD to reduce their discomfort and burden. Family Connections (FC) is a program that has been shown to be effective in reducing burden, depression, and anxiety, and increasing dominance and validating behaviors in relatives of people with borderline personality disorder. However, there are no RCTs that demonstrate the efficacy of the FC program in patients with SBD. Our research team adapted FC for relatives of people with SBD for delivery in the Spanish population (FC-SBD). The FC-SBD program contains 12 two-hour sessions held once a week. The first aim is to verify the efficacy of the FC-SBD intervention for relatives of people diagnosed with SBD in a randomized control trial with a Spanish sample. The second objective is to analyze the feasibility and acceptance of FC-SBD in relatives. The third aim is to analyze whether the changes produced in the psychological variables in the relatives after the intervention are related to changes in the psychological variables of the patients. This paper presents the study protocol.

**Methods:**

The study design consists of a two-arm randomized controlled trial with two conditions: FC-SBD or Treatment as usual optimized (TAU-O). Participants will be relatives of patients who meet DSM-5 criteria for SBD. The caregivers` primary outcome measures will be the BAS. Secondary outcomes will be DASS-21, FES, DERS, QoL. The patient’s primary outcome measures will be the frequency of critical incidents with the family member with SBD. Secondary measures will be the INQ, PHQ-9, OASIS. Participants will be assessed at pretreatment, post-treatment, and 6-month follow-up. The intention-to-treat principle will be used when analyzing the data.

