##### Register of critical incidents with the family member with SBD

This register was developed ad hoc for this study. The questions recorded are the following: frequency of suicide attempts in the past six months, number of days of self-harm in the past six months, number of episodes of verbal/physical violence with caregivers in the past six months; frequency of visits to the psychiatric emergency room in the past six months, frequency of therapy sessions conducted out of schedule in the past six months (face-to-face, phone calls, etc.).

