#### Register of critical incidents with the family member with SBD.

2.Measures of secondary outcomes

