### Data analyses

Regarding data analysis, the CONSORT guidelines [57] will be followed. First, participants' scores in the two conditions before receiving the intervention will be compared to check that there are no significant differences between them on the outcome measures and that they are, therefore, comparable after randomization. ANOVAs will be conducted for continuous variables and Chi-square tests for categorical variables. For outcome measures at post-treatment, we will study whether the assumption of homoscedasticity is met with Leven's test. If this assumption is met, repeated-measures MANOVAs and F-tests will be used to compare the two experimental conditions. If the homoscedasticity assumption is not met, the Brown-Forsythe test will be applied. F-tests for statistical significance will be followed by post hoc comparisons. In particular, Tukey will be used when the homoscedasticity assumption is met, and Games-Howell if the homoscedasticity assumption is not met. Appropriate analyses will also be carried out to calculate intervention effect sizes and confidence intervals. The intention-to-treat principle will be used when analyzing pre- and post-treatment data and at six-month follow-up, using mixed-effects models with full information and maximum likelihood estimation. This method has been recommended due to its flexibility in handling missing data [58]. To complement the MANOVA results and post hoc comparisons, effect sizes will be calculated using the standardized mean difference proposed by Cohen [59]. These effect sizes will be calculated to assess changes within and between groups, all based on a pooled standard deviation. Although per-protocol analyses (only analyses of data from participants who complete treatment) suffer from selection bias, they will also be conducted because they allow conclusions to be drawn about the maximum efficacy of the intervention in participants who are fully compliant with treatment. However, when the trial is over, the analytical methodology for controlled clinical trials will be reviewed before analyzing the data to select the most appropriate analytical procedures.

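### The patients' primary outcome is a register of five different six-month counts with no lead item or composite, and the stated analysis is not built for counts

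*Protocol article*

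**What the plan says.** The Abstract (Methods) states that the patients' "primary outcome measures will be the frequency of critical incidents with the family member with SBD". Under Measures - Patients, the primary outcome is given only by the instrument's name, "Register of critical incidents with the family member with SBD".

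The register's content appears under the relatives' measures, where it is also a secondary outcome. There the article says "This register was developed ad hoc for this study" and lists five items:

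- "frequency of suicide attempts in the past six months, number of days of self-harm in the past six months" (items 1 and 2);
- "number of episodes of verbal/physical violence with caregivers in the past six months" (item 3);
- "frequency of visits to the psychiatric emergency room in the past six months" (item 4);
- therapy contacts outside the schedule, over the same six months (item 5).

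No total score, lead item, weighting or multiplicity rule is stated.

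For outcome measures in general, the Data analyses section says "repeated-measures MANOVAs and F-tests will be used to compare the two experimental conditions", with the Brown-Forsythe test if variances differ. Intention-to-treat analyses use mixed-effects models fitted by maximum likelihood, with no distribution or link named. It adds that "effect sizes will be calculated using the standardized mean difference proposed by Cohen", on a pooled standard deviation. A closing sentence leaves the methods to be reviewed once the trial is over.

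**The concern.** A primary outcome should be one variable, so that a reader knows in advance which result decides the question. Here the name covers five variables of different kinds: events, days and service contacts. The register was made for this study, so no established scoring rule can be presumed. A reduction in any one item could be presented as the patients' primary result. That matters because hypothesis (a) predicts a greater fall in critical incidents under FC-SBD, and the Discussion ties the trial to prevention of suicidal behaviour.

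The second part is the match between the data and the analysis. All five items are counts. The fallback test deals with unequal variances, not with the shape of a count distribution, and a mean difference divided by a pooled SD is an awkward summary of a change in an incident rate.

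**Working it through.** **The plan's own sample size.** The Sample size section gives d = 0.60, two-sided alpha 0.05 and power 0.80. A two-sample t-test needs 44.59 per arm, so 45 per arm and 90 in total, as stated. This figure is for burden in relatives. No sample size or power is given for any patient outcome.

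**Multiplicity.** Inputs: five items (Measures section) and alpha 0.05 (Sample size section). The assumption, which the article does not state, is that each item is tested separately without adjustment.

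- Independent items: 1 − (1 − 0.05)^5 = 1 − 0.7738 = 0.226.
- Pairwise correlation 0.7 between the test statistics: about 0.15.
- Bonferroni upper bound under any dependence: 5 × 0.05 = 0.25.
- One defined endpoint: 0.05.

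**Test behaviour on counts.** The article gives no incident rates, dispersion or number of patients, so all inputs here are assumptions: negative binomial counts, control mean m = 0.3, 1 or 3 per six months, dispersion k = 0.3 or 1, rate ratio 1 or 0.5, and 45 per arm (borrowed from the burden calculation). There were 4,000 simulated trials per scenario. The comparator is a negative binomial likelihood-ratio test with k taken as known, which slightly favours it.

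| k | m | control zeros | t-test, type I error | t-test, power | NB test, power | d for a halved rate |
|---|---|---|---|---|---|---|
| 0.3 | 0.3 | 81% | 5.2% | 17.3% | 20.4% | 0.23 |
| 0.3 | 1 | 64% | 4.1% | 28.0% | 31.5% | 0.30 |
| 0.3 | 3 | 49% | 4.4% | 32.6% | 38.9% | 0.33 |
| 1 | 0.3 | 77% | 4.9% | 24.7% | 26.8% | 0.28 |
| 1 | 1 | 50% | 4.2% | 53.1% | 55.9% | 0.43 |
| 1 | 3 | 25% | 5.4% | 74.6% | 77.5% | 0.53 |

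Type I error of the mean comparison lies between 4.1% and 5.4%. The power loss is about 2 to 6 points.

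**Cohen's d for a halved rate.** Variance of each arm = mean + mean²/k, and d = (m − m/2) / √(average of the two variances).

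- k = 0.3, m = 0.3: variances 0.600 and 0.225, average 0.4125, SD 0.642, d = 0.15/0.642 = 0.23.
- k = 1, m = 3: variances 12 and 3.75, average 7.875, SD 2.806, d = 1.5/2.806 = 0.53.

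The rate ratio is 0.5 in both cases, yet d more than doubles, because it also reflects the mean level and the dispersion.

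**Recall window.** The FC-SBD programme lasts three months (Interventions) and each register item looks back six months. At the end of the programme, about 6 − 3 = 3 months of the recall period precede treatment. At the six-month follow-up the window no longer reaches back before treatment.

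**The case against.** Several counter-arguments have force.

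- **Five unadjusted tests are not stated.** The article plans MANOVA with post hoc comparisons, and the Abstract's phrase could be read as a single total. The 15% to 23% is therefore conditional on separate testing. The ambiguity remains: the MANOVA is not said to span the five items, F-tests are planned beside it, and no total is defined.
- **The loss from mean-based tests is small.** This stands. The table shows no inflation of type I error and only a few points of power. A reader might infer that the planned tests are invalid or that d has no meaning; neither follows. Confidence intervals are planned too.
- **The choice of count model can be left to an analysis plan.** This stands in part: the mixed models fix no distribution. But the article does commit itself to MANOVA, F-tests and Cohen's d for outcome measures, and reviewing methods after the trial does not fix them in advance.
- **Incidents need not be rare.** This stands. The article supports no statement about low rates or many zeros; self-harm days and verbal violence may be frequent.

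Two stronger readings should not be drawn. One is that two relatives reporting on the same patient inflate the patients' primary outcome. Patients are assessed themselves, so shared incidents touch only the relatives' secondary use of the register. The other is that a suicide death would be dropped as ignorable missing data. The register has no item for it, but the article does not say how deaths are recorded or handled, and no magnitude can be given.

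**Conclusion.** The concern holds in a limited form. The heavier part is the undefined endpoint: five different counts share the label of patient primary outcome, with no rule for choosing or combining them. If they are tested separately, the familywise error is about 23% under independence and about 15% at correlation 0.7, against 5% for one endpoint.

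The analysis part is secondary. Under the assumed distributions, the case against mean-based tests is interpretability (d of 0.23 to 0.53 for the same halved rate) and a modest power loss, not false p-values. Those figures rest on assumed rates, dispersion and 45 patients per arm, none of which the article gives for patients.

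The relatives' primary outcome, the BAS, is clearly named and is the only one with a sample size, so the trial's main comparison is not affected. The change should be made, but the trial does not depend on it.

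**What to change.** 1. Name one register item, or one total with a stated scoring rule, as the patient primary endpoint, and make the remaining items secondary.
2. Take it at the six-month follow-up, because the recall period at post-treatment overlaps the time before treatment.
3. Analyse it with one record per patient by negative binomial regression on arm, adjusted for the baseline count, and report a rate ratio with its confidence interval in place of Cohen's d. No observation-time offset is needed, since every item has the same fixed six-month recall.
4. State that the BAS alone carries the confirmatory alpha of 0.05, as the Sample size section already implies.

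The cost is a change of wording made before the data are analysed, and slightly more analysis work. Fewer results can then be labelled primary. No new data are needed.

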**Discussion:**

This study will provide results that confirm the efficacy of the FC-SBD in relatives of people with SBD. These results will also confirm its good acceptance by family members and help us to find out whether it is a good program to improve the prevention of suicidal behaviors in the family environment.

**Trial registration:**

ClinicalTrials.gov ID: NCT05157607. Registered 15 December 2021.

## Background

Suicide is a major public health problem [1]. However, in the past 45 years suicide rates have increased by 60% globally, and suicidal behavior is currently one of the leading causes of death worldwide [2], affecting more than 800,000 people each year [3]. Although suicide prevention is difficult, there is some consensus that prior suicide attempts are the main indicator of completed suicide [4]. Other important risk factors are suicidal ideation, the frequency and number of different methods of self-harm, hopelessness, borderline personality disorder, post-traumatic stress disorder, impulsivity, depression [5], being unemployed, living alone, having low social support, or schizophrenia [6].

Meta-analytic studies indicate that two types of interventions have been shown to be effective in reducing suicide attempts. On the one hand, Dialectical Behavior Therapy (DBT), randomized controlled studies with a two-year follow-up found that DBT was superior to the usual therapy performed by psychologists and psychiatrists who are experts in the treatment of suicide. Thus, DBT reduced suicide attempts by 50% compared to expert suicide therapy [7]. DBT was also more effective in reducing emergencies, doctor visits, and hospital psychiatric care for suicide. Other studies have found that DBT for people with borderline personality disorder (BPD) produced a reduction in the frequency and severity of suicide attempts and non-suicidal self-harm one year after receiving DBT [8]. On the other hand, Cognitive Behavioral Therapy (CBT) [9] has been shown to be effective in reducing the risk of suicide, suicidal ideation, and suicidal behavior in adult patients and in individual [10] and group therapy, reducing the probability of suicide attempts by 50% compared to the usual treatment [11]. However, it is striking that excellent review studies carried out in the adult population [12, 13] do not take into account whether a specific intervention was carried out with families or caregivers and whether they influenced the effectiveness of the treatment.

Suicide attempts are a critical challenge faced by families living with a patient. Family members feel guilty, afraid, and hopeless about the possibility of suicide [14], and this increases the risk of depression and anxiety [15, 16]. Furthermore, it is difficult for family members to recognize suicide attempts, which makes prevention difficult [17]. Family members of people who have attempted suicide are at a high risk of having medical and psychological problems, and, more importantly, they have a higher risk of committing suicide [18]. They tend to report that they are not cared for adequately and that they need help and want to know and understand the treatments the patients receive [14], as well as the skills they may need to relate to them [19].

All of these studies suggest that the needs of family members of people with suicide attempts are not adequately addressed in the current treatments for people with suicide attempts. Therefore, it is necessary to help the relatives of people with suicidal behaviors to reduce the discomfort and burden they experience by giving them information and skills to improve their relationship with patients. In this way, suicide attempts could be prevented / reduced in the family context.

Treatment programs designed specifically for relatives of patients with suicide attempts are scarce. However, action models have been designed to meet the needs of families of people with mental illnesses such as schizophrenia, bipolar disorder, and depression [20], or for relatives of people with eating disorders [21]. In the case of BPD (patients who are at a high risk of suicide attempts), psychoeducation groups can be held for families in order to provide information about the disease and help them understand some of the behaviors of their sick relatives, thus improving the relationship and family coexistence [22].

“Family connections (FC): a program for relatives of persons with BPD” [23] is an adaptation of DBT skills training [24] designed for use with relatives of patients with BPD by professionals or family members who have previously completed a training course in order to lead other groups of family members. The FC program contains 12 two-hour sessions held once a week. The content of the intervention program is divided into six modules and includes psychoeducation about BPD and how it affects family functioning, skills adapted from the DBT program (individual, family, and relational skills, validation exercises, and problem-solving skills), and peer support. All the modules include specific practical exercises and homework assignments. In addition, throughout the FC program, there is a forum where participants can build a support network. Previous non-controlled clinical trials [23, 25–29] found that, after the FC intervention, significant decreases were observed in the subjective experience of burden, perceived discomfort, depression, and grief, and the relatives’ coping strategies improved. These changes were maintained at the three-month follow-up.

Furthermore, in a previous study, Rajalin [17] adapted the FC program in an open trial with relatives of people who had attempted suicide. The relatives had no clinical diagnosis, and the patients were being treated in a suicide prevention program. The results indicated that, after treatment, the general well-being of the family members increased, the feeling of burden and level of discomfort and anxiety decreased, and the relationship with the patient with suicide attempts improved. In addition, the criticism expressed and the expression of emotions decreased. Therefore, the results of this pilot study suggest that the FC program tailored to relatives of patients with suicide attempts may be effective in improving well-being and reducing the burden of illness in relatives. The main limitation of this study is that it is a pilot study with no control group or randomization of the participants.

Therefore, in order to advance in this line of work and improve the clinical situation and quality of life of relatives of patients with suicidal behaviors, it is necessary to have evidence-based intervention protocols focused on the relatives, and to do so it is necessary to submit them to tests of efficacy and efficiency in controlled studies.

This study has several aims. The first objective is to verify the efficacy of the FC intervention for relatives of people diagnosed with Suicidal Behavior disorders (SBD) in an RCT with a Spanish sample of participants from mental health services. The second objective is to analyze the feasibility and acceptance of FC-SBD in relatives of people with SBD. The third objective is to analyze whether the changes produced in the psychological variables in the relatives after the intervention are related to changes in the psychological variables of the patients. The fourth objective is to analyze whether improvements in emotional regulation, validation, control and empowerment, and family functioning predict reductions in burden, anxiety, and depression, and improvements in the quality of life of relatives. Fifth, we will analyze the opinions, preferences, and perceptions of the relatives in both treatment conditions.

We propose the following hypotheses: a) After the intervention, all the participants in the two treatment conditions, Family Connections (FC-SBD) or Treatment as usual optimized (TAU-O), will improve their level of burden, anxiety, depression, quality of life, validation, dominance, and empowerment, and critical incidents in the family environment will be reduced (self-harm, suicide attempts, arguments, etc.). However, the participants in the FC-SBD condition will improve more than those in the TAU-O condition; b) After the intervention, both interventions will have good acceptance by the participants, but the FC-SBD condition will have greater acceptance; c) The changes produced in the psychological variables in the relatives after the intervention will be related to changes in the psychological variables of the patients; and d) The improvement that may occur in the family members with regard to burden, anxiety, depression, and quality of life will be predicted by the improvements in emotional deregulation, validation skills, empowerment, and family functioning.

In this article, we present the study protocol.

### Methods and design

#### Study design

This study is a superiority trial. The study design consists of a two-arm randomized controlled trial (RCT). On the one hand, there will be two conditions: Family Connections (FC-SBD) or Treatment as usual optimized (TAU-O), and family members will be randomized to one of the two groups. Family members will be randomized taking into account that if a patient has more than one family member attending the group, they will be randomized together to be included in the same condition. The effects of the treatment will be measured before starting the group, afterwards, and at the six-month follow-up in order to know whether the effects are maintained in the long term. Figure 1 shows the flow chart. This protocol will follow the CONSORT statement (Consolidated Standards of Reporting Trials, http://www.consort-statement.org) [30, 31] and the SPIRIT guidelines (Standard Protocol Items: Recommendations for Interventional Trials) [32, 33].

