### Sample size

The sample size for this study was generated from effect sizes found in other studies with relatives of people with mental disorders. In the literature, we found a controlled study by Grenyer et al. [22] on a psychoeducational group intervention protocol for family members of people with borderline personality disorder. On the one hand, they found medium to large effect sizes for dyadic adjustment (d=0.78) and family empowerment (d=1.4); on the other hand, they found medium effect sizes for burden (d=0.45) at post-test and 12-month follow-up. The results of these effect sizes are consistent with other studies on psychological treatments for other mental disorders, such as a meta-analysis by Baruch, Pistrang and Barker [34] on psychological interventions for bipolar disorder (Burden, g = -.80). Based on the results of these studies, we expect an effect size of 0.60 because the design of this study consists of two experimental groups. For the calculation of the sample size, we used the G*Power 3.1 software [35], taking into account an alpha of 0.05 and a statistical power of 0.80 in a two-tailed t-test. We need a sample size of 90 participants (45 relatives per condition) to reach an effect size of 0.60 for burden. Finally, we considered possible sample loss during the treatment program. Based on studies of interventions for relatives of people with borderline personality disorder, we expect a 30% dropout rate [17, 23, 27, 36, 37]. Therefore, taking this outcome into account, our study requires a total sample size of 124 participants (62 participants per experimental condition).

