### Procedure

Family members of patients with SBD will be given the opportunity to participate in the study. Once they have completed the informed consent, an expert clinician will carry out the assessment of each participant to check that the inclusion and exclusion criteria are met, and an independent investigator, unaware of the characteristics of the study, will be contacted to carry out randomization. At all times, for randomization purposes, an experimenter from outside the research team will assign each family member to one of the two study conditions (FC-SBD or TAU-O) using a random number software program. The randomization sequence will be concealed from the clinicians participating in the study. Independent assessors will administer the assessment protocol to the participants without being aware of the experimental condition to which they belong (FC-SBD or TAU-O). Patients will also be assessed before starting the intervention programs for relatives. After the assessment has been completed, all the relatives will start to receive the intervention in the condition to which they have been assigned. In the case of patients, they will participate in their current treatment or care. At the end of the intervention, the assessment protocol will be readministered to both relatives and patients, again by independent assessors, and the same thing will be done at the six-month follow-up.

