
### Interventions

#### Interventions with family members

##### Family Connections Protocol for Relatives of Patients with SBD (FC-SBD)

The intervention lasts three months and includes 12 sessions with a weekly two-hour group format.

The FC program [23] is divided into six modules:Module 1: Up-to-date information and research on suicide (Epidemiology, frequency, Risk factors, protective factors).Module 2: Psychoeducation on the development of suicide, explanatory theories, available treatments, comorbidity.Module 3: Emotional regulation skills, skills of acceptance, validation, approach, awareness, and to decrease emotional reactivity.Module 4: Skills to improve the quality of relationships in family interactions (letting go of guilt and anger, acceptance skills in relationships).Module 5: Communication skills and effective self-expression.Module 6: Problem management and making safe plans for crisis management.All the modules include practice exercises, video viewing, and homework assignments. In addition, throughout the program, with the aim of increasing social support, the FC-SBD program provides a forum where participants can stay in touch and share common problems and solutions.

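### Relatives of one patient are randomised together, but the sample size and the named MANOVA, F-tests and post hoc comparisons treat relatives as independent, and no family term is stated for the mixed model

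*Protocol article*

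**What the plan says.** Study design sets the allocation rule: "if a patient has more than one family member attending the group, they will be randomized together to be included in the same condition". The Procedure section describes the mechanism in terms of individuals: an outside experimenter "will assign each family member to one of the two study conditions (FC-SBD or TAU-O) using a random number software program". It does not repeat the rule that relatives of one patient stay together.

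Sample size counts relatives. The calculation was made "taking into account an alpha of 0.05 and a statistical power of 0.80 in a two-tailed t-test", for a standardised difference of 0.60. Its result is: "We need a sample size of 90 participants (45 relatives per condition) to reach an effect size of 0.60 for burden". The only later adjustment is for dropout.

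Data analyses names ANOVAs and chi-square tests at baseline. At post-treatment it names repeated-measures MANOVAs and F-tests, or Brown-Forsythe if variances differ, with Tukey or Games-Howell comparisons. The intention-to-treat analysis is to be done "using mixed-effects models with full information and maximum likelihood estimation". The reason given is flexible handling of missing data, and no random effects are named. The section closes by saying that the choice of methods will be reviewed once the trial has ended, before the data are analysed.

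On delivery, FC-SBD "includes 12 sessions with a weekly two-hour group format". TAU-O adds one three-hour group session to usual care.

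**The concern.** The primary outcome is the Burden Assessment Scale, which asks about the burden of a loved one's illness over the past six months. Two relatives of the same patient rate the same illness over the same period, so a positive correlation between their scores is the natural expectation. Because such relatives always share an arm, the correlation does not cancel in the comparison; it increases the variance of the difference between arms.

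The t-test behind the sample size and the MANOVA and F-tests in Data analyses do not see this. Their standard errors would be too small and their confidence intervals too narrow. The false-positive rate of the burden comparison would exceed 5%, and the trial would hold less information than the sample size section claims. Weekly group treatment in the FC-SBD arm is a second possible source of correlation.

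**Working it through.** **Inputs from the protocol (Sample size):** d = 0.60 (so SD = 1), two-sided alpha 0.05, power 0.80, 45 relatives per arm.

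**Inputs that must be assumed:** mean number of enrolled relatives per patient, m, from 1.25 to 2; family ICC from 0.2 to 0.5. The protocol gives neither, nor an FC-SBD group size or group ICC.

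**Step 1. Reproduce the stated figure.** Two-sample t-test power from the noncentral t distribution, with noncentrality d × √(n/2) and 2n − 2 degrees of freedom:
- 45 per arm: power 0.804
- 44 per arm: power 0.795

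The stated 45 per arm is therefore right if relatives are independent. Power of exactly 0.80 needs about 44.6 per arm, so the tolerable design effect is 45/44.6 ≈ 1.01.

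**Step 2. Family clustering.** Design effect DE = 1 + (m − 1) × ICC; effective n per arm = 45/DE, put back into the same power function. True type I error of a nominal 5% test that ignores clustering = 2 × [1 − Φ(1.96/√DE)].

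| m | ICC | DE | 45/DE | Power | Type I error |
|---|---|---|---|---|---|
| 1.25 | 0.2 | 1 + 0.25 × 0.2 = 1.05 | 42.9 | 0.784 | 0.056 |
| 1.5 | 0.3 | 1 + 0.5 × 0.3 = 1.15 | 39.1 | 0.746 | 0.068 |
| 1.5 | 0.5 | 1 + 0.5 × 0.5 = 1.25 | 36.0 | 0.709 | 0.080 |
| 2 | 0.5 | 1 + 1 × 0.5 = 1.50 | 30.0 | 0.628 | 0.110 |

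This formula supposes families of equal size and is slightly kind when sizes vary. Suppose three patients in four bring one relative and one brings two. The mean is 5/4 = 1.25, but the size-weighted mean is (3 × 1 + 1 × 4)/5 = 1.4. At ICC 0.2, DE is then 1 + 0.4 × 0.2 = 1.08 rather than 1.05, and power is 0.772.

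**Step 3. What group delivery could add.** Assume FC-SBD groups of 10 with ICC 0.05 and no group effect in TAU-O. The FC-SBD arm has DE = 1 + 9 × 0.05 = 1.45, and the average over arms is (1.45 + 1)/2 = 1.225, which alone gives power 0.718. Added to family clustering with m = 1.5 and ICC 0.3 to 0.5, total inflation is 1.15 + 0.225 = 1.375 to 1.25 + 0.225 = 1.475. Power is then 0.67 to 0.64 and naive type I error 0.09 to 0.11. These figures are illustrative only.

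**The case against.** *The mixed model may already handle it.* A reader might infer that every planned analysis ignores families. The protocol does not show that. It leaves the random effects of the mixed model unstated, and family and group terms could sit in an analysis plan that is not at hand. This stands, and it limits the point on the mixed model to saying that no family term is stated and that missing data is the only reason given. It does not rescue the published t-test calculation or the MANOVA and F-tests named beside it.

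*Study design and Procedure do not really conflict.* A reader might see a contradiction between assigning each family member and keeping families together. Both can be true if co-attending relatives share one assignment. Procedure omits the rule rather than denying it, so this is a clarification. It is still worth making, because Procedure is where the allocation steps are described.

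*The loss may be small, or offset.* The keep-together rule is conditional, and nothing says how often a patient brings several relatives. At the low end of the range, power is 0.78 and type I error 0.056. Baseline information could also recover power. With an assumed pre-post correlation r and variance factor 1 − r², a design effect of 1.15 gives power of about 0.82 at r = 0.4 and 0.86 at r = 0.5. So it would be too strong to say that the planned model certainly has less than 0.80 power. But the protocol's 0.80 comes from an unadjusted t-test, and baseline adjustment does not correct the type I error of a test that ignores the unit of randomisation.

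*Group clustering is less certain than family clustering.* The protocol does not say that the FC-SBD groups are closed, how large they are, or that group membership is recorded. It supports only a possible addition.

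**Conclusion.** The point holds in a limited form. The protocol fixes family-wise allocation, a sample size that assumes independent relatives, and between-arm tests that assume the same. These do not fit together. The direction is certain under any positive within-family correlation: the unadjusted tests are anti-conservative, and the stated t-test loses its 0.80 power once the design effect passes about 1.01.

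The size cannot be fixed from the protocol. On the assumed 1.25 to 2 relatives per patient and ICC 0.2 to 0.5, power is 0.78 to 0.63 and true type I error 0.056 to 0.11. If few patients bring more than one relative, the effect lies at or below the mild end. A large loss, or a mixed model that ignores families, is not established.

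**What to change.** - In Study design, state that the family (patient) is the unit of randomisation, and repeat the keep-together rule in Procedure.
- Make the mixed model the primary burden analysis in place of the MANOVA and F-tests, with a random intercept for family. Family-clustered standard errors with a small-sample correction are an alternative. If Kenward-Roger degrees of freedom are chosen, fit by REML rather than the maximum likelihood now named.
- Examine therapy-group clustering in FC-SBD as a sensitivity analysis. At an assumed 10 per group, 62 relatives make about six groups, too few to estimate a group variance well.
- Record family and therapy-group identifiers for every relative. The protocol does not say that this is done.
- Restate power under explicit family-size and ICC assumptions, as a range.

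The cost is some wording and two identifiers per relative. Intervals will be slightly wider and the stated power less favourable. No participants need be added for valid inference. Restoring 0.80 for the unadjusted t-test would need more relatives, and that is a separate decision for the sponsor.
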